## LIST OF ABBREVIATIONS AND RELEVANT DEFINITIONS

|                 |                                                                                                                                                                                                                               |
|-----------------|-------------------------------------------------------------------------------------------------------------------------------------------------------------------------------------------------------------------------------|
| ABR      | General Assessment and Registration form (ABR form), the application form that is required for submission to the accredited Ethics Committee; in Dutch: Algemeen Beoordelings- en Registratieformulier (ABR-formulier) |
| AE       | Adverse Event                                                                                                                                                                                                          |
| AR       | Adverse Reaction                                                                                                                                                                                                       |
| ARTS     | ARthritis Treatment Satisfaction                                                                                                                                                                                       |
| CA       | Competent Authority                                                                                                                                                                                                    |
| CCMO     | Central Committee on Research Involving Human Subjects; in Dutch: Centrale Commissie Mensgebonden Onderzoek                                                                                                            |
| CSI      | Central Sensitization Index                                                                                                                                                                                            |
| CV       | Curriculum Vitae                                                                                                                                                                                                       |
| DSMB     | Data Safety Monitoring Board                                                                                                                                                                                           |
| EU       | European Union                                                                                                                                                                                                         |
| EudraCT  | European drug regulatory affairs Clinical Trials                                                                                                                                                                       |
| GCP      | Good Clinical Practice                                                                                                                                                                                                 |
| GDPR     | General Data Protection Regulation; in Dutch: Algemene Verordening Gegevensbescherming (AVG)                                                                                                                           |
| HADS     | Hospital Anxiety and Depression Scale                                                                                                                                                                                  |
| HALF-MIS | High Amplitude Low Frequency Music Impulse Stimulation                                                                                                                                                                 |
| IC       | Informed Consent                                                                                                                                                                                                       |
| ICD-10   | International Statistical Classification of Diseases and Related Health Problems, 10th edition                                                                                                              |
| IMDD     | Investigational Medicinal Device Dossier                                                                                                                                                                               |
| METC     | Medical research ethics committee (MREC); in Dutch: medisch-ethische toetsingscommissie (METC)                                                                                                                         |
| NRS      | Numeric pain Rating Scale                                                                                                                                                                                              |
| PDI      | Pain Disability Index                                                                                                                                                                                                  |
| QoL      | Quality of Life                                                                                                                                                                                                        |
| QST      | Quantitative Sensory Testing                                                                                                                                                                                           |
| (S)AE    | (Serious) Adverse Event                                                                                                                                                                                                |
| SPC      | Summary of Product Characteristics; in Dutch: officiële productinformatie IB1-tekst                                                                                                                                    |
| Sponsor  | The sponsor is the party that commissions the organisation or performance of the research, for example a pharmaceutical                                                                                                |

company, academic hospital, scientific organisation or investigator.  
A party that provides funding for a study but does not commission it is not regarded as the sponsor, but referred to as a subsidising party.

|              |                                                                                                                   |
|--------------|-------------------------------------------------------------------------------------------------------------------|
| SUSAR | Suspected Unexpected Serious Adverse Reaction                                                              |
| UAVG  | Dutch Act on Implementation of the General Data Protection Regulation; in Dutch: Uitvoeringswet AVG        |
| UTAUT | Unified Theory of Acceptance and Use of Technology                                                         |
| VNS   | Vagal Nerve Stimulation                                                                                    |
| VAM   | Vibroacoustic Music Therapy                                                                                |
| VAT   | Vibroacoustic Therapy                                                                                      |
| WHO   | World Health Organisation                                                                                  |
| WMO   | Medical Research Involving Human Subjects Act; in Dutch: Wet Medisch-wetenschappelijk Onderzoek met Mensen |

## SUMMARY

**Rationale:** Chronic musculoskeletal pain is a disabling condition with huge individual and societal impact in Western society. A considerable amount of patients have decreased functional and biological capacities and lack resilience to stand current treatment standards, including surgery, or medication to handle their pain optimally. Besides, current treatments suffer from side effects. There is a high demand on the development of non-invasive treatments without side effects.

To explain chronic pain syndromes, neuroplasticity has been a point of focus the last decade. Discovering the mechanism of neuroplasticity also suggests the development of new pain relief modalities, that address neuroplasticity and the neuromatrix effectively. Previous studies found that abdominal Pacinian bodies, are related to neuroplasticity via the vagal nerve. Sound impulses below the human ear's frequency (limit about 20 Hz), may be considered as infrasound, activate the Pacinian bodies. Infrasound waves pass without significant attenuation through the air, solid and liquid media. It appears that infrasound with high amplitude affects the human sensory system (via the Pacinian bodies) via Vagal and splanchnic stimulation. Currently, Vagal Nerve Stimulation (VNS) is being used for treatment of resistant cases of eg. pain and depression. Substantial amounts of evidence for this effect have been gathered although the precise mechanism is still unknown. VNS, however, requires an intrusive intervention and has some negative side effects, because of efferent stimulation.

HALF-MIS (High Amplitude Low Frequency Music Impulse Stimulation)', is an innovative treatment modality aimed at stimulation of the Pacinian bodies with the use of infrasound to stimulate vagal activity. Previously, substantial effects were demonstrated on reduction of depression. It is, however, expected to be effective when used in pain management.

Hypotheses: 1. HALF-MIS is a safe and well tolerated intervention. 2. HALF-MIS decreases pain significantly compared to a placebo treatment in elderly patients suffering from chronic musculoskeletal pain. 3. Central sensitization mediates the effect of HALF-MIS.

**Study design:** Placebo controlled pilot study

**Study population:** 60 patients ( $\geq 65$  year) with chronic musculoskeletal pain.

**Intervention (if applicable):** Each patient will have a schedule consisting of 3 weekly treatments over the course of 3 weeks. Each session will last 20 minutes and 27 seconds according to the length of the music. In all of the eight visits, patients in the treatment group will undergo the HALF-MIS treatment. For this treatment the patient sits relaxed in a chair and gets a belt around the waist with a built-in vibro-tactile unit which delivers vibro-stimulation. For the music patients get a headphone. An iOS app is used to administer the stimuli, synchronize the audio and log the patients' treatments. Patients in the placebo group will follow the same procedure, but without the vibro-stimulation.

**Main study parameters/endpoints:** Self reported pain (NRS), Quality of life (EuroQol-5D-3L).

**Nature and extent of the burden and risks associated with participation, benefit and group relatedness:** In total there are 10 visits: 1 screening, 8 treatments and 1 follow-up. During the screening, patients will be asked about their medical history and get a physical examination to determine inclusion. During the first, last en follow-up visits patients have to fill in questionnaires. The first and last treatment visit, patients also undergo quantified sensory testing measurements. Previous trials in depression consistently reported positive effects of treatment and no lasting side effects. In some trials, symptoms such as dizziness and nausea are reported but they are always dose related and pass after the treatment session. Since patients get a pain treatment, the pain intensity might decrease during and/or after the treatments.

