## 1. INTRODUCTION AND RATIONALE

Chronic musculoskeletal pain is a disabling condition with huge individual and societal impact in Western society (1). With an aging society, the relevance for finding suitable and effective treatment modalities also significantly increases for the elderly. These patients frequently suffer from co-morbidities and accompanying poly-pharmacy alongside the chronic pain syndrome. A considerable amount of patients have decreased functional and biological capacities and lack resilience to stand current treatment standards, including surgery, or medication to handle their pain optimally. Besides, current treatments suffer from side effects. There is a high demand on the development of non-invasive treatments without side effects, alleviating pain in elderly and frail patients suffering from musculoskeletal pain.

To explain chronic pain syndromes, the ability of neurostructures to change their reaction when exposed to prolonged stimuli (neuroplasticity) has been a point of focus the last decade. Discovering the mechanism of neuroplasticity also suggests the development of new pain relief modalities, that address neuroplasticity and the neuromatrix effectively (2). Previous studies found that the Pacinian bodies, located in the abdominal cavity, are related to neuroplasticity via the vagal nerve. These bodies are built with free nerve endings protected by multiple keratin layers. While the exact function of these bodies is still ambiguous, the Pacini body frequency response curve is determined by a maximum output at afferent stimulation with a vibration frequency of approx. 240 Hz (3). In principle, however, there is no lower frequency limit as a single stimulation with pressure leading to deformation of the body capsule resulting in an afferent Vagal action potential.

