#### Treatment

Each patient will have a schedule consisting of 3 weekly treatments over the course of 3 weeks. Each session will last 20 minutes and 27 seconds according to the length of the music. In all of the eight visits, patients in the treatment group will undergo the HALF-MIS treatment. For this treatment the patient has to sit in a chair and get a belt around the waist with a built-in vibro-tactile unit which delivers vibro-stimulation. For the music, patients wear a headphone. An iOS app is used to administer the stimuli, synchronize the audio and log the patients' treatments. Patients in the placebo group will follow the same procedure, but the vibro-stimulation is programmed without any infrasound. The frequencies used are around 240 Hz, that will excite the Pacinian corpuscles in the skin but not penetrate the abdominal wall to elicit a VNS stimulation. In this way, the patient will feel vibrations of the skin, but the actual treatment is not given.

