## 5. TREATMENT OF SUBJECTS

### 5.1 Investigational product/treatment

HALF-MIS is primarily a vibratory and auditory stimulus within the range of normal life exposures. As this is a non-drug, non-invasive, non-electrical treatment, NO serious side effects are associated with HALF-MIS.

Similar low frequency exposure has been a part of some music therapy concepts, namely VAT (Vibroacoustic Therapy) and VAM (Vibroacoustic Music Therapy) for decades. In this context low frequency exposure has been investigated (as a black box) in the treatment of various conditions such as pain, depression and spasticity. The trials consistently reported positive effects of treatment and no lasting side effects. In some trials, symptoms such as dizziness and nausea are reported but they are always dose related and pass after the treatment session. We encountered two cases of lens luxation in patients exposed to a shaking chair installation with extremely powerful 5 Hz shaking. This exposure is not considered comparable to the HALF-MIS bass exposure, as it has no content of frequencies below 20 Hz.

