## 6. INVESTIGATIONAL PRODUCT

### 6.1 Name and description of investigational product(s)

The RemPulse system consists of a set of components: A controller (currently in the form of an iPad) connected via cables and a standard adapter, the RemPulse app installed on the aforementioned controller, a transducer belt, an ACU and a set of headphones. The patient puts on the transducer belt and headphones, assumes a comfortable position (e.g. reclining or lying down), starts the treatment.

The patient is exposed to vibrations (ca. 20-100Hz, 0-150W) in the abdomen from the transducer belt on their belly, inducing a feeling of comfort in the brain, which, trials suggest, reduces pain and depression symptoms. The 0-150W denotes the power supplied to the transducer and not the actual power induced in the patient's tissue, which is significantly less. Throughout the treatment session, the patient listens to a relaxing audio track in the headphones; this is harmonically and rhythmically aligned with the aforementioned vibrations. Without the music/said alignment, the vibrations feel quite odd - even disturbing to some - and don't have the same effect.

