#### *Configuration and functional elements*

Throughout the clinical investigation, RemPulse will only be used in a single hardware configuration without any other variants:

- The ACU is connected to the supply mains through a detachable power supply cord. The appliance coupler is a PowerCON type and will only fit into one socket on the ACU.
- The iPad is connected through an adaptor connecting to the iPad's Lightning port.
- The adapter is connected to the ACU through an HDMI signal cable and a USB Lightning power supply cable. The former only fits in the only HDMI socket on the ACU and the adapter. The latter only fits in the only USB socket on the ACU; it also connects to the adapter's Lightning port. It can accidentally also be connected directly to the iPad, in which case the system won't work; it will just cause the iPad to recharge.
- The headphones are connected to the 3.5mm minijack connector on the iPad, using a detachable cable, the other end of which is connected to the headphones with a proprietary connector. There are no other minijack connectors in the system; neither are there any small, round DC power plugs or similar that could be mistaken for a minijack connector.
- The transducer belt has a fixed cord with a SpeakON connector, which is connected to the only compatible socket in the system.

The RemPulse app is installed on the controller iPad:

1. After installation, the RemPulse app downloads the treatment track, which provides the audio and vibrational stimulation signals. This may take a few minutes, depending on network speed and is only needed once.

2. When the patient is ready (i.e. wearing the belt and headphones and in a relaxed position), the treatment is initiated via the start button on the screen; the button subsequently changes into a stop button. If needed, the treatment can be stopped by pressing the stop button. Otherwise, the treatment continues until the track has finished after about 20 minutes. It is not possible to pause and resume the treatment.
3. Regardless how the treatment ends, the screen again assumes the ready state with a start button, and another treatment can be initiated.
4. The audio volume can be turned up and down as needed using a standard volume slider.
5. The treatment intensity can be adjusted using the + and - buttons between levels 1 through 10, the latter being the highest intensity.

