#### *Functionality*

- The iPad administers the signals to the headphones and vibrational transducer, the former of which are connected directly to the iPad. The vibrational signal is sent to the ACU.
- The ACU consists of a digital signal converter, a 280W audio amplifier, a medical isolation transformer and various power components. The digital signal converter changes the digital signal from the iPad into an analogue, low-frequency signal, which is then sent to the amplifier and out to the transducer. All components are powered from the ACU. Mains supply is fed through the isolation transformer, which then powers the amplifier, the signal converter and USB power to the iPad adapter.
- The transducer belt consists of a large belt made from synthetic fabric, which is strapped around the belly and lower back of the patient. On the belt, a mounting plate is affixed on which a vibrational transducer is mounted by the researcher, who received training in standard application of HALF-MIS treatment. The transducer is a 400W (maximum, typical signal is about 100W) 4Ω low-frequency vibrator designed to transmit frequencies between 5Hz and 200Hz. During operation, the mounting plate is roughly centred on the patient's bellybutton, held tight by the belt. Importantly, the plate must not press against the ribs and hip bones, as this will cause discomfort from the vibrations. Throughout the treatment session, vibrations harmonically and

rhythmically aligned with the audio, are transmitted from the transducer through the belly and into the patients' abdominal cavity.

The headphones provide audio at whatever level is comfortable to the patient and thus function normally.

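### The protocol describes the placebo and active stimulation in contradictory ways, so infrasound does not separate the arms on its own text and the placebo is not shown to be deliverable

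*Protocol*

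**What the plan says.** **Placebo.** The Summary (Intervention) states: "Patients in the placebo group will follow the same procedure, but without the vibro-stimulation". Section 3 (Treatment) says that in the placebo group "the vibro-stimulation is programmed without any infrasound", and continues: "The frequencies used are around 240 Hz, that will excite the Pacinian corpuscles in the skin but not penetrate the abdominal wall". Section 8.2 (Blinding) agrees with section 3 that placebo patients feel vibration, of a kind that should not produce vagal stimulation. It gives no frequency.

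**Hardware.** Section 6.1 (Functionality) describes the transducer as a "low-frequency vibrator designed to transmit frequencies between 5Hz and 200Hz". Section 6.1 (Configuration and functional elements) adds that "RemPulse will only be used in a single hardware configuration without any other variants".

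**Active treatment.** The Summary (Rationale) and section 1 present HALF-MIS as acting through infrasound, which they place below about 20 Hz. Section 6.1 says: "The patient is exposed to vibrations (ca. 20-100Hz, 0-150W) in the abdomen from the transducer belt on their belly". Section 5.1 reports two cases of lens luxation under a very strong 5 Hz shaking chair and sets them aside: "This exposure is not considered comparable to the HALF-MIS bass exposure, as it has no content of frequencies below 20 Hz".

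**Receptor.** Section 1 states that "the Pacini body frequency response curve is determined by a maximum output at afferent stimulation with a vibration frequency of approx. 240 Hz".

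**The concern.** A placebo-controlled trial needs one description of what each arm receives. Here the statements about the control stimulus, the feature that separates it from the active stimulus, and the reason for discounting a safety signal cannot all be true together.

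Three things depend on them:

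- **Blinding.** Pain on the NRS is self-reported and is the primary endpoint for objective 2 (section 10.1). A belt that does not vibrate, compared with one that vibrates the abdomen for about 20 minutes per session, would undermine the patient blinding claimed in section 8.2 and leave the NRS open to expectation effects.
- **Interpretation.** If the arms do not differ in infrasound, neither a positive nor a null result says anything about infrasound.
- **Safety.** Tolerability and safety form the first listed objective (section 2), in patients aged 65 or over. The reason given for treating the lens luxation cases as not comparable should agree with the rest of the protocol.

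**Working it through.** The protocol gives no power calculation or other figure to reproduce on this point. The check compares the statements with each other and with the stated frequency ranges.

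1. **Is the placebo belt silent or vibrating?** The Summary removes the vibration. Section 3 supplies vibration at around 240 Hz, and section 8.2 also has the patient feel it. The two descriptions exclude each other. Two sections of the body agree, so the Summary is the outlier.

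2. **Can the placebo of section 3 be delivered on the stated hardware?**
   - Placebo frequency (section 3): around 240 Hz.
   - Transducer design range (section 6.1): 5 to 200 Hz.
   - Excess: 240 − 200 = 40 Hz; 240 / 200 = 1.20, so 20% above the upper limit.
   - Section 6.1 allows one hardware configuration and describes no other transducer. It describes the track that the app downloads for treatment but no placebo counterpart.
   - Result: the protocol does not show that this signal reaches the patient as described. If output at that frequency were weak, the placebo would move towards the silent belt of the Summary.

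3. **Does infrasound separate the arms?**
   - Infrasound (Summary, section 1): below about 20 Hz.
   - Active exposure (section 6.1): about 20 to 100 Hz.
   - Active content below 20 Hz (section 5.1): none.
   - Placebo (section 3): no infrasound; around 240 Hz.
   - Result: the active range starts where infrasound ends. On these passages neither arm contains infrasound, so its absence cannot be what makes the control a control. The transducer's range extends down to 5 Hz, so the hardware description does not exclude infrasound. The exclusion comes from the stated exposure and from section 5.1.

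4. **Do the safety and efficacy statements agree?** In section 5.1, the grammatical subject of the clause about content below 20 Hz is loose. It can sensibly mean only HALF-MIS, because the other exposure named is 5 Hz shaking. The reason for setting the two cases aside is therefore that HALF-MIS has no content below 20 Hz. The efficacy rationale says that it works through content below about 20 Hz. If either statement holds, the other fails.

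**The case against.** The best defence is that the body of the protocol does give a usable contrast. Sections 3 and 8.2 agree on a vibrating placebo, and with section 6.1 the reader has numbers for both arms: about 20 to 100 Hz against around 240 Hz. Those are different stimuli whatever they are called. Much of this stands. A reader might infer that the tested contrast is undefined; the documents support only that it is described in contradictory ways.

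Other stronger readings also fail:

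- **That patients will be unblinded.** This follows only if the Summary sentence overrides sections 3 and 8.2, and nothing says that it does.
- **That the placebo cannot be delivered.** A design range is not a statement of zero output above it. No roll-off is given, and the placebo frequency is itself approximate.
- **That the placebo stimulates the target receptor.** Section 1 does place the peak Pacinian response at about 240 Hz. However, section 3 argues that this vibration reaches corpuscles in the skin and does not pass the abdominal wall, and the stated target is abdominal. One may doubt that, but it is not a contradiction, and the documents cannot settle it.
- **That the between-arm comparison is invalid.** The objectives in section 2 concern the effect of HALF-MIS on pain and central sensitization. None of them tests infrasound or vagal activity.
- **That patients face a risk of lens luxation.** The text shows only that the reason for discounting those cases conflicts with the rationale. Section 5.1 also describes the chair exposure as extremely powerful.

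Two further points count for the defence. Both 20 Hz limits are approximate, so the firm exclusion of infrasound rests on section 5.1. Section 6.6 refers dosage to the device dossier, which is not among the documents and may specify the signal. Neither point removes the conflicts inside the protocol, and correcting the Summary sentence alone would leave items 2 to 4 of the working in place.

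**Conclusion.** The concern holds as a contradiction in how the arms are described. The Summary conflicts with sections 3 and 8.2 on whether the placebo vibrates. The placebo frequency lies 20% above the stated range of the only transducer described. Infrasound, offered as both the mechanism and the dividing line between the arms, is absent from both on the figures in sections 5.1 and 6.1. The same figure supports the safety argument and undercuts the efficacy rationale.

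The inconsistency touches every between-arm comparison in the planned 60 patients. It does not prevent a randomised comparison of HALF-MIS with placebo, but as the text stands a difference, or the lack of one, could not be attributed to infrasound.

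This conclusion rests on two readings: that the section 5.1 clause refers to HALF-MIS, and that the placebo is given through the transducer of section 6.1. The second is likely, since the procedure is otherwise the same and the placebo is described as a matter of programming, but it is not stated outright. The correction is needed before the protocol is used, because it bears on blinding, interpretation and safety. It is inexpensive.

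**What to change.** The sponsor should:

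1. Reconcile the Summary (Rationale and Intervention), section 1, section 3 (Treatment), section 5.1, section 6.1 and section 8.2 (Blinding) to one description of each arm. The description should come from the existing track and device specifications, or from a simple check of output on the trial hardware.
2. Confirm that the placebo signal, as then described, can be delivered on that hardware.
3. Word the efficacy conclusion as the difference between the two tracks actually delivered, and mention infrasound only if the reconciled description supports it.
4. Re-check the lens luxation statement in section 5.1 against the same description.

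Which description of the stimulation is right is for the sponsor to decide.

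The cost is a small amount of checking and a wording amendment, with no change to patients or visits. More work would follow only if the check shows that the placebo cannot be delivered as described.
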